## Abstract

**Background:**

Trauma-focused treatments for posttraumatic stress disorder (PTSD) are commonly delivered either once or twice a week. Initial evidence suggests that session frequency affects treatment response, but very few trials have investigated the effect of session frequency. The present study’s aim is to compare treatment outcomes of twice-weekly versus once-weekly sessions of two treatments for PTSD related to childhood trauma, imagery rescripting (ImRs) and eye movement desensitization and reprocessing (EMDR). We hypothesize that both treatments will be more effective when delivered twice than once a week. *How* session frequency impacts treatment response, whether treatment type moderates the frequency effect, and which treatment type and frequency works best for whom will also be investigated.

**Methods:**

The IREM-Freq trial is an international multicenter randomized clinical trial conducted in mental healthcare centers across Australia, Germany, and the Netherlands. We aim to recruit 220 participants, who will be randomized to one of four conditions: (1) EMDR once a week, (2) EMDR twice a week, (3) ImRs once a week, or (4) ImRs twice a week. Treatment consists of 12 sessions. Data are collected at baseline until one-year follow-up. The primary outcome measure is clinician-rated PTSD symptom severity. Secondary outcome measures include self-reported PTSD symptom severity, complex PTSD symptoms, trauma-related cognitions and emotions, depressive symptoms, dissociation, quality of life, and functioning. Process measures include memory, learning, therapeutic alliance, motivation, reluctance, and avoidance. Additional investigations will focus on predictors of treatment outcome and PTSD severity, change mechanisms of EMDR and ImRs, the role of emotions, cognitions, and memory, the optimization of treatment selection, learned helplessness, perspectives of patients and therapists, the network structure of PTSD symptoms, and sudden treatment gains.

**Discussion:**

This study will extend our knowledge on trauma-focused treatments for PTSD related to childhood trauma and, more specifically, the importance of session frequency. More insight into the optimal session frequency could lead to improved treatment outcomes and less dropout, and in turn, to a reduction of healthcare costs. Moreover, the additional investigations will broaden our understanding of how the treatments work and variables that affect treatment outcome.

**Trial registration:**

Netherlands Trial Register NL6965, registered 25/04/2018.

**Supplementary Information:**

The online version contains supplementary material available at 10.1186/s13063-021-05712-9.

## Background

Posttraumatic stress disorder (PTSD) can develop after exposure to a traumatic event. PTSD is a chronic and severe mental disorder characterized by four main clusters of symptoms, including re-experiencing the traumatic event, avoidance of trauma-related stimuli, negative feelings or thoughts, and increased arousal [1]. Based on meta-analytic reviews and practice guidelines, trauma-focused cognitive behavior therapy (TF-CBT) and eye movement desensitization and reprocessing (EMDR) are recommended as first-line treatments for PTSD [2, 3]. However, the efficacy of traditional (stand-alone) PTSD treatments for patients with childhood trauma-related PTSD (Ch-PTSD) is more uncertain [4–7]. Individuals with Ch-PTSD are characterized by more complex symptoms, such as interpersonal difficulties, emotional regulation problems, impaired self-concept, and memory and attention difficulties [5, 7–9]. A meta-analysis on psychological treatments for Ch-PTSD found evidence that patients with Ch-PTSD can be treated effectively with trauma-focused treatments [7]. However, research into the effectiveness of treatments for patients with Ch-PTSD is limited as existing studies on the effectiveness of PTSD treatments mainly focus on survivors of adult-onset trauma, resulting in an underrepresentation of survivors of childhood-onset trauma [7, 10].

A recent randomized clinical trial (RCT) (IREM) found promising results for two treatments for Ch-PTSD, namely imagery rescripting (ImRs) and EMDR [11]. ImRs involves the patient recalling the start of the traumatic experience and, subsequently, imagining an intervention that changes the course of events to a more positive outcome aimed at satisfying the needs of the patient [12, 13]. In EMDR, the therapist instructs the patient to focus on a traumatic memory, composed of images, emotions, cognitions, and physical sensations, while the therapist concurrently provides a form of active distraction (e.g., following the back and forth movements of the finger of the therapist) [14]. There are indications that both treatments are effective treatments for patients with PTSD related to childhood trauma. In a meta-analysis on treatments for Ch-PTSD, three RCTs evaluating the effectiveness of EMDR were included [7]. It was found that EMDR was effective in treating PTSD as a consequence of childhood trauma, yielding moderate to high effect sizes. Although ImRs has been less studied to date [15], a recent RCT into the effectiveness of ImRs as a stand-alone treatment for Ch-PTSD concluded that ImRs was effective and highly acceptable [16]. Moreover, in the IREM trial evaluating the comparative effectiveness of EMDR and ImRs, large treatment effects were found for both treatments between baseline and one-year follow-up (i.e., *g* = 2.24 for ImRs and *g* = 1.86 for EMDR on the Clinician Administered PTSD Scale for DSM-5) and treatment dropout was limited to 7.7%. These results were favorable compared to the results found in a meta-analysis on treatments for Ch-PTSD [7]. This meta-analysis found an average effect size for pre-treatment to long-term follow-up (≥ 6 months) of *g* = 1.56 and an average dropout of 22.3%. In discussing the positive outcomes of the treatments in the IREM trial, the authors proposed that the low dropout rate and large symptom reduction might be related to the twice-weekly session frequency of each treatment condition. In contrast, in routine mental health care, trauma-focused treatments are commonly delivered once a week [17]. More insight into the impact of session frequency on treatment outcome is therefore needed.

There are indications that session frequency might be related to the effectiveness of trauma-focused treatments for PTSD. Gutner et al. [17] have examined the association between session frequency and treatment outcome of cognitive processing therapy (CPT) and prolonged exposure (PE) among patients with PTSD. They concluded that a higher session frequency was related to better treatment outcome. In addition, other studies have examined the impact of massed treatments (i.e., daily treatment) compared to weekly treatments for PTSD [18–21]. Results suggest that a more intensive format is similarly effective [18–20] or even more effective [21] compared to treatment once a week. Moreover, the massed treatment leads to a faster reduction in PTSD symptoms. The findings that a higher session frequency is related to better outcomes are consistent with findings based on a meta-analysis on treatments for depression [22] and naturalistic studies across different diagnostic groups (e.g., depression, anxiety disorders, personality disorders) [23, 24]. Furthermore, a RCT among depressive patients demonstrated that delivering treatment twice a week is more effective than delivering treatment only once a week (difference in effect size *d* = 0.55 [25]). However, research into the (causal) effect of session frequency on treatment outcome in PTSD patients is scarce, and there is limited understanding of the mechanisms involved.

Several mechanisms underlying the presumed positive impact of a higher session frequency on treatment outcome in PTSD patients have been hypothesized, including the role of memory and learning, therapeutic alliance, and reducing avoidance [17, 18, 23, 26, 27]. One possible explanation is related to learning processes. Trauma-focused treatments involve the processing of corrective information, which is then stored in memory [12, 28, 29]. New insights might be strengthened by more frequently providing corrective information [26]. This is congruent with previous studies in the field of neurobiology that have shown that the continued survival of neurons, which is realized by their reactivation within a time window of maximum 5 days, is important for learning [30]. This suggests that delivering treatment sessions twice a week (i.e., less than 5 days in between sessions) is more beneficial compared to sessions once a week (i.e., more than 5 days in between sessions). Moreover, Bruijniks et al. [27] hypothesized that a high session frequency might lead to a better recall of the content of the previous sessions, which increases the efficiency and effectiveness of the treatment. In addition, Ehlers et al. [18, 19] pointed out that patients with (Ch-)PTSD have problems with concentration and memory and an intensive treatment format may help patients and therapists to keep the therapeutic material in mind.

An alternative hypothesis is that more frequent sessions have a positive effect on the therapeutic alliance, which in turn affects treatment outcome [23, 27]. It has been proposed that when the contact with the therapist is more frequent, the relationship between the patient and therapist develops more rapidly [27]. In addition, less frequent sessions may attenuate the stability of the therapeutic alliance, because both therapist and patient may feel less connected with each other and less actively involved in the therapy [23]. Research among PTSD patients has shown that the therapeutic alliance is positively related to treatment outcome (e.g., [31–33]). Moreover, the importance of the therapeutic relationship to facilitate change was underscored by Ch-PTSD patients receiving EMDR or ImRs [34].

Finally, more frequent treatment sessions may help PTSD patients to reduce their avoidance of confronting trauma memories [17]. A more intensive treatment format may reduce the opportunity for anticipatory fear or anxiety and avoidance behavior between sessions, which might, in turn, reduce resistance and increase the motivation of patients [26, 35, 36]. In qualitative interviews with Ch-PTSD patients and therapists about their experiences with EMDR or ImRs, some patients and therapists reported that the frequent sessions (i.e., twice-weekly sessions) indeed helped to prevent avoidance behavior and to maintain motivation [34, 37]. In addition, a brief treatment format may help with making the treatment more acceptable to patients since they only need to tolerate distress related to the trauma processing for a short period of time [18, 26].

### Current study

In conclusion, initial evidence suggests that session frequency has an impact on the effectiveness of trauma-focused treatments for PTSD. However, there is a paucity of randomized trials comparing the effects of twice-weekly versus once-weekly treatment sessions, and no trials have examined this issue in Ch-PTSD. This article describes the study design of IREM-Freq, a follow-up study of the IREM study, which compared the effectiveness of twice-weekly EMDR and ImRs for Ch-PTSD [38].

#### Primary objective

The primary objective of the current study is to compare treatment outcomes of twice-weekly versus once-weekly sessions of EMDR and ImRs for adult patients with PTSD related to childhood trauma. We will, therefore, perform an international, multicenter RCT conducted in a routine clinical setting. We hypothesize that both treatments will be more effective when delivered twice a week compared to once a week.

#### Secondary objectives

The IREM-Freq study has several secondary objectives. These include investigating (1) the comparative effectiveness of EMDR and ImRs, (2) whether treatment type (i.e., EMDR versus ImRs) moderates the effect of session frequency, (3) the hypothesized change mechanisms underlying the effects of session frequency on treatment outcome (i.e., memory and learning, therapeutic alliance, motivation, and reluctance and avoidance), (4) the (differential) change mechanisms of EMDR and ImRs, (5) potential predictors of treatment outcome and PTSD severity, (6) the role of emotions, cognitions, and memory in the change in PTSD symptoms, (7) the impact of trauma-focused treatments on learned helplessness, (8) the optimization of treatment selection through identifying patient characteristics that predict treatment response across treatment types (EMDR and ImRs) and treatment frequencies (twice-weekly and once-weekly sessions), (9) the perspectives of patients and therapists on the treatments, (10) the network structure of PTSD symptoms, and (11) sudden treatment gains.

## Methods/design

### Design

The study is an international, multicenter superiority RCT with a two by two factorial design, with an equal allocation ratio. The first factor is treatment frequency (twice a week versus once a week), and the second factor is the treatment type (EMDR versus ImRs). The study is registered at the Netherlands Trial Register, part of the Dutch Cochrane Center, with registration number NL6965, and complies with the World Health Organization Trial Registration Data Set. Modifications to the protocol will require a formal amendment to the protocol. The amendments will be examined by the ethics committees of each country and, if approved, included in the trial registration. This trial adheres to the SPIRIT guidelines and methodology [39], see Additional file 1: Appendix A for the SPIRIT checklist. For an overview of the study design, including the recruitment, randomization, assessments, and treatments, see Fig. 1.

**Fig. 1 Fig1:**
[figure not shown]
Flow chart of the study design. EMDR = eye movement desensitization and reprocessing; ImRs = imagery rescripting. *A waitlist assessment is included for patients with a waitlist period of more than five weeks before the start of treatment

### Setting

The study will be carried out in routine clinical settings in eleven mental healthcare centers in the Netherlands (Abate, Enkhuizen; GGZ Noord-Holland-Noord, Heerhugowaard; GGZ Oost Brabant, Helmond; PsyQ, Amsterdam and Beverwijk; and Sinai Centrum, Amstelveen), Germany (University of Lübeck, Lübeck; LMU Munich, Munich; and University of Münster, Münster), and Australia (Centre for Psychotherapy - Hunter New England Mental Health Service, Newcastle and the Sexual Assault Resource Centre, Perth).

### Eligibility criteria

Patients are eligible if they (1) are between 18 and 70 years old; (2) have a primary diagnosis of PTSD as assessed by the Structural Clinical Interview for DSM-5-Clinician Version or Research Version (SCID-5-CV/RV); (3) have experienced the worst traumatic event (defined according to the DSM-5) before the age of 16 and agree that this trauma will be the focus of treatment; (4) have been experiencing PTSD symptoms for longer than 3 months; and (5) have an adequate proficiency in the language of the center or an adequate proficiency in the English language in case the center has English-speaking research assistants and therapists. Patients will be excluded if they (1) have experienced a trauma less than 6 months ago; (2) meet criteria for a current substance use disorder with a moderate or severe severity level (i.e., more than four symptoms), diagnosed with the SCID-5-CV/RV (after 6 weeks of abstinence, participation is possible); (3) fulfill the criteria of a psychotic disorder, diagnosed with the SCID-5-CV/RV; (4) have been diagnosed with the SCID-5-CV/RV with bipolar I disorder; (5) have acute suicide risk; (6) have an IQ below 80; (7) experience serious neurological problems (e.g., dementia); (8) are scheduled to start another form of PTSD treatment; (9) have received PTSD focused treatment within the past 3 months; (10) use benzodiazepine (after 3 weeks of abstinence, participation is possible); or (11) are not able to attend the treatment sessions of both randomization possibilities (i.e., 12 sessions of 90 min within 8 weeks and 12 sessions of 90 min within 16 weeks). In addition, patients will not start treatment unless their medication use has been stable for at least 3 weeks. Finally, patients are not allowed to start any form of psychological treatment or medication between the screening period and 24 weeks after the start of the study treatment (non-PTSD focused supportive treatment may be continued during the screening and waitlist period).

### Sample size

We aim to include 220 participants with about an equal number of participants (*n* = ± 55) in each of the four conditions (i.e., EMDR once a week, EMDR twice a week, ImRs once a week, and ImRs twice a week). We expect a dropout percentage of 10%, which is a conservative estimate given the 7.7% dropout found in the IREM study, the predecessor of the current study [11]. Each site intends to recruit at least 20 patients.

A sample size of *N* = 200 is sufficient to have 94% power to detect a medium effect size (i.e., Cohen’s *d* = .50) between frequency groups (i.e., twice-weekly versus once-weekly sessions of EMDR and ImRs) at post-test or follow-up, assuming equal sample sizes and a two-tailed significance level of *p* < .05, and based on a *t*-test. In addition, the study has 80% power to detect a group difference with an effect size of Cohen’s *d* = .40. Moreover, in case of a significant treatment by frequency interaction, with *N* = 200 power is 80% to detect an effect size of *d* = 0.57 for a comparison of frequency effects within a treatment at a two-tailed significance level of .05 (*t*-test at post-test or follow-up, assuming equal sample sizes of 50 per frequency).

### Procedure: recruitment, informed consent, assessments, blinding, and participant timeline

Patients are recruited from the participating mental healthcare centers. Patients with a (suspected) primary diagnosis of PTSD due to childhood trauma are invited to participate in the screening process to assess for eligibility to participate in the study based on the inclusion and exclusion criteria. The screening process will start after patients have received verbal and written information about the study and signed an informed consent form (see Additional file 1: Appendix B). First, to assess for syndrome and personality disorders, the SCIDs are administered by trained clinicians or research assistants. Second, an interview is conducted to assess the patient’s motivation, availability, and treatment interfering factors. Furthermore, trauma history is assessed using the Life Events Checklist for DSM-5 (LEC-5), including additional items to screen for emotional abuse, emotional neglect, and physical neglect. The LEC-5 is administered once during the screening process to identify the nature and extent of traumatic events. In addition, the worst traumatic event that occurred before the age of 16 and complies with the definition of a traumatizing event according to the DSM-5 (i.e., index trauma) is identified. Finally, the worst traumatic memory of the index trauma and a presently held negative self-referencing belief (i.e., encapsulated belief) are determined. The index trauma, worst memory, and encapsulated belief are used to determine the focus of other measures (i.e., PTSD Checklist for DSM-5 (PCL-5) and the imagery interview).

After the screening assessments are completed, a final check of the inclusion and exclusion criteria is performed by the junior investigator and the patient is randomized by an independent staff member of the sponsor. After randomization, the site investigator of the center is informed of the patient’s allocated treatment condition and searches for a suitable therapist, taking into account the availability of the patient and the preference of the patient for a male or female therapist. At the same time, the baseline assessment (T1) is administered by a research assistant blinded to the patient’s allocated condition. If the time between the start of the treatment and the baseline assessment is more than 5 weeks, an additional assessment (i.e., waitlist assessment) is conducted before the patient starts with the treatment. After the baseline assessment (and, if applicable, the waitlist assessment) is completed and a therapist has been found, the patient starts the treatment. The session frequency of the treatment (i.e., twice a week or once a week) will be revealed to the patient with the invitation for the first session, but the treatment type (i.e., EMDR or ImRs) is not communicated to the patient until the first treatment session.

After treatment has started, patients are re-assessed at four different time points over the course of 1 year: (1) T2: 6 to 8 weeks after the start of the treatment (after six sessions in the once-weekly frequency condition, or after 12 sessions in the twice-weekly frequency condition), (2) T3: 12 to 16 weeks after the start of the treatment (after 12 sessions in the once-weekly frequency condition, or 14 weeks after the start of the treatment in the twice-weekly frequency condition), (3) follow-up 1: 24 weeks after the start of the treatment, and (4) follow-up 2: 52 weeks after the start of the treatment. Patients who discontinue their treatment or deviate from the protocol will be encouraged to continue the assessments. The assessments, including a combination of interviews and computer-based self-report questionnaires, are conducted by a trained research assistant who is blind to the patient’s treatment condition and audio-recorded. Unblinding of research assistants is not permissible. Due to the nature of the interventions, blinding of patients and therapists is not possible. In addition, starting with session 2, the patient and therapist fill out questionnaires before the start of each session to steer the treatment (patient: PCL-5) and to assess potential mediators (patient and therapist: mediator items). Before the fourth and eighth session, the patient and therapist complete an additional questionnaire assessing their memory of the previous session. The questionnaires are completed independently in separate rooms. The study does not involve the collection of biological specimens. An overview of the assessments is presented in Table 1, excluding the candidate predictors of (differential) treatment response that are assessed only once at baseline.

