#### Primary outcome

##### PTSD severity

The primary outcome is the change in the severity of the DSM-5 PTSD symptoms between the baseline and follow-up 1 assessments, assessed with the Clinician Administered PTSD Scale for DSM-5 (CAPS-5 [54]). The CAPS-5 is a structured interview consisting of 30 5-point Likert scale items ranging from 0 (absent) to 4 (extreme/incapacitating) rating the 20 DSM-5 PTSD symptoms in the past month. In the current study, the CAPS-5 assesses responses to all traumatic events that have been identified with the LEC-5. The CAPS-5 has demonstrated good reliability and validity [55–57].

The assessment period of the CAPS-5 (i.e., past month) at the T3 assessment overlaps with the treatment period in the once-weekly frequency condition. Therefore, we chose to focus on change between baseline and follow-up 1 instead of baseline and T3 since the follow-up 1 assessment takes place several weeks after treatment has finished and does not overlap with the treatment period (i.e., administered 8–12 weeks after treatment has finished in the once-weekly frequency condition and 16–18 weeks after treatment has finished in the twice-weekly treatment condition).

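### The baseline CAPS-5 is taken after randomisation, and nothing requires it to be finished before the invitation that reveals session frequency

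*Protocol article*

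**What the plan says.** The section on procedure, blinding and participant timeline fixes the order of events. Screening comes first and includes an interview that covers the patient's availability. After that, "a final check of the inclusion and exclusion criteria is performed by the junior investigator and the patient is randomized". Next, "After randomization, the site investigator of the center is informed of the patient’s allocated treatment condition and searches for a suitable therapist", with the patient's availability and preferred therapist gender considered. Then: "At the same time, the baseline assessment (T1) is administered by a research assistant blinded" to the arm. Treatment begins once T1 is done and a therapist is available. A further waitlist assessment is added when more than 5 weeks separate T1 from the start of treatment.

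The same section sets out what the patient is told and when. The session frequency "will be revealed to the patient with the invitation for the first session"; the treatment type "is not communicated to the patient until the first treatment session". The Allocation section repeats both rules. Unblinding of research assistants is ruled out.

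Under PTSD severity: "The primary outcome is the change in the severity of the DSM-5 PTSD symptoms between the baseline and follow-up 1 assessments", using the CAPS-5. Under Interventions, Format, later sessions are booked in session 1 unless that has already happened.

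**The concern.** A baseline is safest when it cannot be affected by allocation, and measuring it before randomisation guarantees that. Here T1 runs alongside the therapist search by someone who knows the arm. The CAPS-5 is an interview that rates what the patient reports, so a blinded rater does not help if the patient already knows the schedule. Frequency is the primary comparison, and it is also the item disclosed first.

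If knowing the frequency moved baseline reports differently in the two arms, part of the estimated effect on change would be an artefact of the baseline. The self-report measures and candidate predictors collected at T1 would be open to the same influence. Separately, anyone who leaves between randomisation and T1 is in the intention-to-treat set without a baseline.

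**Working it through.** **1. The sequence and who knows the arm.**

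1. Eligibility check, then randomisation: only the independent staff member knows.
2. The site investigator is told and starts the therapist search.
3. In parallel, T1: the rater is blinded, and by plan the patient has not been told.
4. Invitation to session 1: the patient learns the frequency.
5. Session 1: the patient learns the treatment type.

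T1 must precede the start of *treatment* (step 5). No sentence says that it must precede the *invitation* (step 4). The Format section also permits booking before session 1, and a booked once- or twice-weekly pattern reveals the frequency. The intended order may well be 3 before 4, but the text does not require it.

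**2. The plan's own figures.** Sample size section, two-sided 0.05, two-sample t-test with noncentrality d√(n/2):

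- n = 100 per arm, d = 0.50: 0.50 × √50 = 3.54, power 94.0% (stated 94%).
- n = 100 per arm, d = 0.40: 0.40 × √50 = 2.83, power 80.4% (stated 80%).
- n = 50 per arm, d = 0.57: 0.57 × √25 = 2.85, power 80.6% (stated 80%).
- 220 less 10% = 198, or 99 per arm: 93.8% at d = 0.50 and 80.0% at d = 0.40.

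All reproduce, and none depends on when T1 is taken.

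**3. What a baseline shift would do (illustration; the inputs are assumptions).** Let p be the share of an arm aware of its frequency before T1, and s the mean shift in their score in SD units. The differential shift is b = p₂s₂ − p₁s₁. If awareness and shift are the same in both arms, b = 0 and the contrast does not move. If only one arm shifts, 10% aware × 0.2 SD gives 0.02, and 30% × 0.5 SD gives 0.15.

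With baseline–follow-up correlation ρ and 100 per arm:

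- Raw change: bias b, SE = √(2(1 − ρ) × 2/100).
- Baseline-adjusted: bias ρb, SE = √((1 − ρ²) × 2/100).
- Type I error = Φ(bias/SE − 1.96) + Φ(−bias/SE − 1.96).

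Example, b = 0.10 and ρ = 0.5, raw change: SE = √0.02 = 0.141, ratio 0.707, error Φ(−1.253) + Φ(−2.667) = 0.105 + 0.004 = 10.9%.

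| b (SD) | ρ | Raw change: bias, error | Adjusted: bias, error |
|---|---|---|---|
| 0 | any | 0, 5% | 0, 5% |
| 0.05 | 0.3 | 0.05, 6.0% | 0.015, 5.1% |
| 0.05 | 0.7 | 0.05, 7.4% | 0.035, 6.4% |
| 0.10 | 0.5 | 0.10, 10.9% | 0.05, 6.9% |
| 0.20 | 0.3 | 0.20, 22.3% | 0.06, 7.3% |
| 0.20 | 0.7 | 0.20, 44.7% | 0.14, 28.3% |

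The article specifies mixed regression without saying how baseline enters, so both columns are shown. Adjustment reduces the bias but does not remove it.

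**4. Missing baselines.** Each 1% of 220 lost between randomisation and T1 is 0.01 × 220 = 2.2 patients. The article gives no rate for this interval.

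**The case against.** The two people who produce the CAPS-5 score are both meant to be unaware of the arm: the rater throughout, and the patient until the invitation. The site investigator knows, but the article does not make that person the T1 rater. Availability is already assessed at screening, and patients who cannot attend both schedules are excluded, so the therapist search need not involve a telling conversation with the patient. Booking before session 1 is allowed but is not the default. An invitation presupposes a therapist, and some patients wait more than 5 weeks after T1, so for many T1 will come well before any invitation. All of this stands, and it makes the risk modest.

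Running T1 alongside the search also has a plausible advantage, because it keeps the baseline close to treatment. A reader might infer that the order serves no purpose. The article states no reason, but it does not rule this one out.

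It can also be said that patients who withdraw before T1 do not yet know their frequency, so differential loss is not expected, and that they may give no later data either. That is fair as far as bias goes. But with T1 first, those who leave before T1 would never be randomised, and those who leave afterwards would at least have a baseline.

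Finally, linking the invitation to T1 might be left to the full protocol. The post-randomisation position of T1, however, is a procedure that the article states, not an omitted detail.

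**Conclusion.** The point holds as a weakness in sequencing. One of the two primary measurements is scheduled after allocation, and the safeguards stop short of requiring T1 to be complete before the frequency is disclosed or sessions are booked.

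A reader might go further and infer that baseline scores are in fact contaminated, or that the contrast is biased by some particular amount. The document supports neither. It gives no awareness rate, no shift and no correlation, so the ranges above show only how the result depends on those assumptions. They apply only if the shift differs between the frequency arms; with no difference the error rate stays at 5%. No sample size, alpha or power figure is affected, and no two passages contradict each other. The change is worth making because it is cheap, it concerns the primary endpoint, and the Trial status section says recruitment is still open.

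**What to change.** By amendment, for patients still to be randomised, complete T1 after the final eligibility check and before the independent staff member draws the allocation. This protects the baseline and also removes the group of randomised patients without one.

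At minimum, state that the allocation is withheld from the site, and the invitation from the patient, until T1 is logged as complete. This protects the baseline but leaves the withdrawal gap between randomisation and T1.

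For patients already randomised, report how many had T1 after the invitation, by frequency arm, and how many were randomised but never had T1.

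The cost is a somewhat later therapist search and possibly a longer interval from T1 to treatment. The existing waitlist assessment covers that interval when it exceeds 5 weeks, although more patients might then need one. Sample size, alpha, power and treatment are unchanged.
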